Another objective will be to identify the pathways that could lead to overweight/obesity and higher energy intake/expenditure. Some of the candidates include lower income leading to higher consumption of nutritionally poor products leading to obesity, marital status leading to higher energy intake, among many other possibilities. These options will be tested by adjusting Structural Equation Models (SEM), where each of the pathways that lead to the dependent variables will be tested independently for statistical significance. We will also calculate the Standardized Root Mean Square Residual (SRMR) for each of the final structural models to assess its goodness-of-fit, with the objective of selecting the models with the pathways that best fit the data. Finally, given the multicentric nature of the sample, we will also fit structural models with clustered standard errors to relax the assumption of independence of observations within clusters of regions and countries.

Further specific sub-projects will depend on the results and associations found for the initial analyses. Some of these sub-projects include analyses of micronutrient ingestion, snack consumption and the determinants of regular physical exercise levels. Other projects will follow depending on the results and associations observed in the main analyses. Some of the individual variables regarding dietary and physical activity patterns will likely be aggregated, depending on their interdependent relationships and previous studies in the literature, by applying factor analysis. The final datasets compiled from each country will be standardized into groups of variables and categories and sent to the coordinating center in Brazil. Descriptive statistical analyses, multilevel analyses, and structural equation models will be performed with R 3.2.0, MLwiN 2.29, and Stata 13, respectively.

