The study also has several potential weaknesses. The ELANS is currently a cross-sectional study with all of the inherent limitations of this type of design. This means that it will be able to explore correlates of dietary intake, physical activity and obesity, but not its causal determinants. One of the issues of the ELANS is the variations in SEL questionnaire between countries since its format was based on the legislative requirements or established local standard layouts. That may reduce the validity of cross-country comparisons. The ELANS countries span a wide range of health, social and economic indicators; however, the results of the study may not be directly generalizable to other countries. Nevertheless, no study has evaluated the nutritional statuses and physical activity patterns of adolescent and adult populations in Latin American using a standardized methodology across a consortium of several participating countries. This study will provide a unique dataset from Latin America that will enable cross-country comparisons of nutritional status that focus on both energy intake and expenditure. The findings of this study should affect the planning of health policies and programs that are designed to control nutritional inadequacies and low levels of physical activity, and their consequences, as well as the local and cultural adaptation of these policies and programs for implementation in Latin American countries.

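### SRMR, the only fit index named for choosing among structural models, does not penalise added paths and is identical for equivalent models with reversed arrows

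*Protocol article*

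**What the plan says.** After the multilevel models, the Analysis plan section of the protocol article adds a further aim: "Another objective will be to identify the pathways that could lead to overweight/obesity and higher energy intake/expenditure". Two examples are given, both with a direction already assumed: "Some of the candidates include lower income leading to higher consumption of nutritionally poor products leading to obesity", and "marital status leading to higher energy intake, among many other possibilities".

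Two rules follow. The first is a test of each path: "each of the pathways that lead to the dependent variables will be tested independently for statistical significance". The second concerns fit: "We will also calculate the Standardized Root Mean Square Residual (SRMR) for each of the final structural models to assess its goodness-of-fit", and its purpose is stated as "with the objective of selecting the models with the pathways that best fit the data". SRMR is the only fit index named. The same paragraph plans clustered standard errors, because observations within regions and countries are not independent.

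The Discussion states the limit of the design: "it will be able to explore correlates of dietary intake, physical activity and obesity, but not its causal determinants".

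**The concern.** The article names an index and says what it is for, so this is a stated choice and not a detail left to a fuller plan. SRMR is a reasonable description of how far a model's implied covariances lie from the observed ones. It is poorly suited to choosing between models with different numbers of paths, because it charges nothing for an added path. It also depends only on the implied covariances, so two models with opposite arrows and the same implied covariances cannot be told apart.

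At stake is whether a selected model reflects the data or the selection rule. An over-full model could be presented as the best-fitting account of how obesity arises, and a direction assumed at the start could be taken as supported by the fit. The Discussion expects the findings to inform health policy and programmes, so either misreading could matter.

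**Working it through.** The article gives no SRMR value or cut-off, so there is no figure to reproduce. The check concerns how the rule behaves.

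**Inputs.** n = 9,000 is the projected sample (Analysis plan). The design effect of 1.75 comes from Sampling procedures. Assumptions not in the documents: continuous normal variables, path coefficients of −0.2 and +0.2 in the three- and four-variable chains, random coefficients with standard deviation 0.25 in six-variable models, and maximum likelihood fitting.

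**Definition.** SRMR = √(mean of the squared standardised residual covariances over the lower triangle, diagonal included). The number of parameters does not appear.

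**Direction, exactly.** Take X = income, M = diet, Y = obesity. In the chain X→M→Y every element is reproduced except the X–Y correlation, whose implied value is r_XM × r_MY. With 6 distinct elements,

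SRMR = |r_XY − r_XM r_MY| / √6.

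This is unchanged when X and Y are swapped, so the reversed chain has the same SRMR. One simulated sample of 9,000 gave:

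| Model | SRMR | Chi-square |
|---|---|---|
| X→M→Y | 0.004077 | 0.972 |
| Y→M→X | 0.004077 | 0.972 |
| X←M→Y | 0.004077 | 0.972 |
| X→M←Y, with X and Y uncorrelated | 0.012193 | 7.443 |
| X→M→Y plus X→Y (saturated) | 0 | 0 |
| Fully reversed, saturated | 0 | 0 |

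The first three models are equivalent and cannot be separated. The fourth reverses one arrow, implies different covariances and is separated. Direction is therefore hidden within an equivalence class, not in every case.

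**Number of paths.**

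- True three-variable chain, 2,000 samples: adding the null path X→Y lowered SRMR in 100 %. BIC preferred the larger model in 0.3 %. This agrees with theory: one extra path is accepted when a chi-square on 1 degree of freedom exceeds ln 9,000 = 9.10, which has probability 0.0025.
- True four-variable chain, 1,000 samples: three successive null paths lowered SRMR in 89.1 %, 88.9 % and 100 %. The last of these saturates the model.
- Six variables, random and often misspecified models, 1,000 data sets: the saturated model had SRMR 0 every time. Adding one path to a nested model raised SRMR in 129 of 1,000 and did not raise it in the other 871. A non-nested model with one more path had the higher SRMR in 399 of 1,000.

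**What the path tests do.** Assume a two-sided 5 % level and removal of non-significant paths; the article states neither. A null path then survives about 5 % of the time instead of always. Weak real associations still pass: the smallest significant standardised coefficient is about 1.96/√9,000 = 0.021. Using the effective sample size 9,000/1.75 = 5,143, it is 1.96/√5,143 = 0.027. Every surviving path, however small, comes free of charge when SRMR then compares models.

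**Why the replacement needs a clustering adjustment.** Suppose a design effect of 1.75 also applied to the path statistic. An unadjusted BIC would then accept a null path when a chi-square on 1 degree of freedom exceeds 9.10/1.75 = 5.20, with probability 2.3 %. Scaling the statistic by 1.75 and using ln 5,143 = 8.55 brings this back to 0.35 %.

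**The case against.** The strongest reply is that SRMR is not the whole rule. Every path is also tested for significance, and SRMR is computed for models described as final, which suggests that pruning comes first. This largely stands. It means the 100 % figure describes SRMR acting alone and not the whole procedure. It does not rescue SRMR as the selector: the article does not say that non-significant paths are dropped, models that survive testing can still differ in size, and a significance test says nothing about direction.

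A second reply is that no fit index settles direction. That is correct. Equivalent models have the same likelihood, so with equal numbers of parameters they have the same BIC. The remedy for direction lies in how results are described, not in the index.

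A third reply is that the Discussion already disclaims causal conclusions and that the objective is worded tentatively. This also stands. A reader might infer a flat contradiction between the two sections, but the documents support only a need to carry the Discussion's caution into the reporting of the paths.

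A reader might also infer that SRMR always picks the model with the most paths, or can never distinguish an arrow from its reverse. The simulations refute both. Nor does the open candidate list, or the absence of a multiplicity rule, count against the plan here: a condensed article may leave these to the fuller document.

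**Conclusion.** The point holds in limited form. As the only index named for selection, SRMR has no complexity penalty and cannot separate covariance-equivalent models. Preference for the fuller model is guaranteed only against a saturated candidate. It is a strong tendency for nested models (about 87 % to 100 % of the comparisons run) and not a rule for non-nested ones. The path-wise tests reduce the effect to an extent that depends on how they are applied.

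The percentages rest on assumed coefficients and continuous normal data, whereas overweight and obesity are treated as dichotomous in the multilevel models. The absence of a penalty, the zero for a saturated model and the equality for equivalent models do not depend on the chosen coefficients. Severity is low to moderate: the structural models serve a further objective and do not affect the primary descriptive outcome.

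**What to change.** - Keep SRMR as a descriptive check of absolute fit, and remove it as the basis for selection.
- Choose among the theory-specified candidate models with a parsimony-adjusted criterion such as BIC.
- Adjust that criterion for clustering, for example through an effective sample size or a design-based scaled statistic, in keeping with the clustered standard errors already planned.
- Report selected paths as associations consistent with an assumed direction, in line with the Discussion, and say that equivalent models with other directions fit equally well.

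The cost is a few sentences of plan wording and slightly more analysis work, with no new data. Selected models may be sparser, so some weak paths may be left out. A split-sample confirmation is not required. It would halve the sample to about 4,500, or roughly 4,500/1.75 = 2,571 effective. For paths using accelerometer data (40 % of the sample, 3,600 people) it would leave about 1,800, or 1,800/1.75 = 1,029 effective.

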## Discussion

The ELANS is a comprehensive cross-sectional multicenter investigation of the nutritional and physical activity statuses of adolescents and adults in 8 Latin American countries.

An important strength of the ELANS study concerns the number of participating countries from different regions in Latin America including countries that lack data on dietary intake and physical activity level of its population. In addition, the data set allows unique comparisons of dietary and physical activity patterns, as all measurements were obtained according to standard methodology and protocols in all participating countries and all countries started the fieldwork in very near time. The objective measures of physical activity with accelerometer from subgroups of respondents, further enriches the data set. Another strength of the study is the selection and adaptation of a food composition database to make cross-country nutritional intake comparisons. Standardization at the food and nutrient levels will likely minimize systematic and random errors in nutrient intake estimations because between-country comparisons are particularly prone to error when different food composition tables are used to estimate dietary intake.

The study also has several potential weaknesses. The ELANS is currently a cross-sectional study with all of the inherent limitations of this type of design. This means that it will be able to explore correlates of dietary intake, physical activity and obesity, but not its causal determinants. One of the issues of the ELANS is the variations in SEL questionnaire between countries since its format was based on the legislative requirements or established local standard layouts. That may reduce the validity of cross-country comparisons. The ELANS countries span a wide range of health, social and economic indicators; however, the results of the study may not be directly generalizable to other countries. Nevertheless, no study has evaluated the nutritional statuses and physical activity patterns of adolescent and adult populations in Latin American using a standardized methodology across a consortium of several participating countries. This study will provide a unique dataset from Latin America that will enable cross-country comparisons of nutritional status that focus on both energy intake and expenditure. The findings of this study should affect the planning of health policies and programs that are designed to control nutritional inadequacies and low levels of physical activity, and their consequences, as well as the local and cultural adaptation of these policies and programs for implementation in Latin American countries.
